# BACKGROUND

Worldwide, there are 36.7 million people living with HIV (PLWH) with a marked increase in uptake of antiretroviral therapy (ART) and a steep decline in numbers of AIDS-related deaths. However globally the leading cause of death is from cardiovascular disease (CVD) with the majority of deaths occurring in developing countries. The path to atherosclerotic CVD progression, mainly coronary artery and cerebrovascular disease, remains silent until advanced stages and the end result is significant disability or death.

An estimated 16.6% of South Africans aged between 15-49 years are living with HIV, of which 23.2% are women of reproductive age. A reduction in HIV-related mortality among women of reproductive age in South Africa is largely attributed to increased access to antiretroviral treatment resulting in non-communicable diseases such as diabetes, cerebrovascular disease and hypertension surpassing HIV as the leading causes of death. Although there appears to be higher risk of CVD in HIV infected men, international studies have shown that the risk of CVD in HIV infected women is significant. As more HIV infected South African women of reproductive age access antiretroviral treatment resulting in potential increased life expectancy, there remains a paucity of data for non-communicable co-morbidities in this vulnerable population group.

In addition to the well-recognized traditional risk factors for CVD in HIV uninfected women, there is increasing evidence of HIV-related chronic inflammation and immune activation and certain antiretroviral drugs that contribute to the increased presence of metabolic syndrome in PLWH. The presence of metabolic syndrome defined by elevated blood pressure, glucose, dyslipidaemia and abdominal obesity, doubles the risk of cardiovascular disease. A systematic review has shown that the mean prevalence of metabolic syndrome among PLWH in Africa was 30.5%. Local studies have demonstrated an increase in obesity in the first 3 years after HIV acquisition and that obesity is more pronounced in black females compared to males. Investigators have further demonstrated that South Africa is facing an epidemic of hypertension, and that there is a high prevalence of concurrent hypertension and HIV highlighting the need for improved integration of management guidelines. The Heart of Soweto study has shed light on the rising incidence of acute coronary syndrome and other cardiovascular diseases in Black South Africans.

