# research design and methods

## Overview

1. Study Setting: Umlazi/Philasande Research Clinic and Gateway Umlazi Clinic
2. Study Design: This study is a prospective two-arm, quasi-experimental design comparing a primary health care intervention plan with usual care.
3. Target Population: HIV infected women attending PHC
4. Study population: HIV infected women aged from 18 to 49 years of age and receiving HIV care at PHC clinics.
5. Inclusion criteria

- HIV infected women
- On ART for at least 1 year
- Equal to/older than 18 years of age
- Equal to/younger than 49 years of age
- Plans to remain in the study catchment area for at least 3 years

1. Exclusion criteria

- Participant declines study participation

1. Sampling

• Size of sample

400 HIV-infected women consisting of an intervention arm of 200 women co-enrolled in the PROMOTE study at the Umlazi CRS (see method of sampling for details), and a control arm of 200 women receiving HIV care at the PHC. With a 20-30% estimated prevalence of metabolic syndrome in people living with HIV without any specific intervention in the risk factor modification of cardiovascular disease and a proposed 10-15% estimated incidence of metabolic syndrome in the intervention arm, 132 participants per arm would allow for 80% power. An additional 10% can be added to allow for loss to follow-up. The larger proposed sample size will allow for external validity / generalizability.

- Method of selecting sample

Two HIV-infected female cohorts will be matched for receipt of ART duration >1 year and for age will be compared in the study. Method of selection will be via convenience sampling.

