- **Intervention group**: The prevalence of CVD risk factors will be determined by data collection through history taking, physical examination, and laboratory and radiology investigations as per the data collection tool. CVD risk assessment will be performed annually using a combination of the WHO and International Society of Hypertension cardiovascular risk prediction (WHO/ISH) and the DAD CHD equation. The intervention proposed is a modified WHO PEN algorithm incorporated into HIV management guidelines at study entry. Trends in all risk factors will be monitored, and new risk factors identified, with 6 monthly intervention during the first year, and annually for three years thereafter.
- **Control group**: Following informed consent, data will be collected from the participants ARV clinic medical chart as per the data collection tool. Standard of care HIV management and primary health care will be provided by public sector clinic staff according to current national guidelines. No study investigations or study questionnaires will be carried out at entry visit until the final study visit. There will be regular telephonic follow up with the participants to maintain study retention. Chart review data collection at 6 monthly intervals. CVD risk factors, as per outcomes described above, will be measured by the study at a single 3 year final study visit. Information obtained will be conveyed to the clinic staff for further management if required.

1. Plan for Data handling/processing

- Data will be analysed using SAS or SPSS software

1. Statistical methods

- Descriptive statistics-continuous variables will be represented by means, medians, prevalence, standard deviation.

The categorical variables will be represented by N+%

- Analytic statistics

The continuous variables will be compared by use of t-tests or Wilcoxon rank sum tests.

The categorical variables will be compared using Chi sq or Fisher’s exact test/

- Logistic regression will be applied to identify predictors of cardiovascular disease between the two arms, and between those participants who exhibit atherosclerosis by carotid intima thickness and those who don’t.

1. List of possible confounders

- Women in the intervention group are already enrolled in a study with controlled settings. These women may have commenced ART with a higher baseline CD4 counts.
- Multivariate logression analyses will be utilized in order to control for confounders.

1. List of associations to be measured

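### The sample size rests on a prevalence of metabolic syndrome in one arm against an incidence in the other; both arms need one measure, and the power needs restating

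*Protocol*

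**What the plan says.** In the protocol's Overview of design and methods, the sample-size item under Sampling gives the rate without intervention as a prevalence ("With a 20-30% estimated prevalence of metabolic syndrome in people living with HIV without any specific intervention in the risk factor modification") and the rate with intervention as an incidence ("a proposed 10-15% estimated incidence of metabolic syndrome in the intervention arm"). From this pair it concludes that "132 participants per arm would allow for 80% power". It adds that "An additional 10% can be added to allow for loss to follow-up" and plans 200 women per arm. The incidence has no time period and no at-risk denominator.

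Four other places bear on the point:

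- **Exclusion criteria.** The only exclusion is declining to take part, so women who have metabolic syndrome at entry are enrolled.
- **Plan for data collection, control group.** "No study investigations or study questionnaires will be carried out at entry visit until the final study visit".
- **Schedule of evaluations.** The control chart-review column has BMI, systolic blood pressure and lipids, but no waist circumference or fasting glucose. At month 36 all of these are measured in both arms. The intervention arm is also measured from month 0.
- **Statistical methods.** Categorical variables are compared by chi-square or Fisher's exact test, with regression for confounders. Metabolic syndrome is not named there, nor in the objectives, the variable list or the association table.

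**The concern.** Prevalence at month 36 counts every woman who has the syndrome, including those who had it at entry. Incidence counts only new cases, normally among women free of it at entry. With identical arms and no intervention effect, the first exceeds the second unless enough baseline cases remit.

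The data schedule does not resolve the mismatch. The Background defines the syndrome by blood pressure, glucose, lipids and abdominal obesity. Controls have no glucose or waist measurement before month 36, so their baseline status, and hence their incidence, cannot be established. The intervention arm can supply an incidence.

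Two things are at stake. An analysis that copied the planned contrast would remove prevalent cases from one arm only. And the 132-per-arm figure is tied to a difference that may partly reflect the change of measure, so it does not show what power the trial has for a like-for-like comparison.

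**Working it through.** **Inputs from the protocol.** Prevalence 20-30%; incidence 10-15%; 132 per arm for 80% power; 200 per arm planned; 10% loss, leaving 200 × 0.9 = 180.

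**Assumptions.** Two-sided alpha 0.05 (alpha is not stated in this protocol), and the remission rates used in step 2. Step 2 also extends the 3-year incidence down to 5%. Step 3 assumes control incidences of 20-30%.

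**1. Reproducing 132.** The usual formula for two proportions is

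n = [1.96·√(2p̄(1−p̄)) + 0.842·√(p₁(1−p₁)+p₂(1−p₂))]² / (p₁−p₂)².

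For 28% vs 14%: p̄ = 0.21, and n = (1.129 + 0.478)² / 0.14² = 131.7, so 132. Other pairs inside the two ranges give:

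| Without vs with intervention | n per arm for 80% power | Power at 132 | Power at 200 |
|---|---|---|---|
| 30% vs 15% | 121 (134 with continuity correction) | 84% | 95% |
| 28% vs 14% | 132 | 80% | 93% |
| 25% vs 12.5% | 152 | 74% | 90% |
| 20% vs 10% | 199 | 62% | 80% |
| 20% vs 15% | 906 | 19% | 26% |

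So 132 is reproducible, but only for some pairs, and only by treating both rates as the same kind of proportion.

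**2. What the mixed contrast does under no effect.** Give both arms the same baseline prevalence b, 3-year incidence i among unaffected women, and remission fraction r of baseline cases. Then

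month-36 prevalence = (1−r)·b + (1−b)·i.

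Compare this in 180 controls with i among the 180·(1−b) at-risk women in the intervention arm, by a two-proportion z-test.

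Example: b = 20%, i = 10%, r = 0.
- Control prevalence = 0.20 + 0.80 × 0.10 = 28%, against 10% in 144 women.
- Pooled proportion = (50.4 + 14.4)/324 = 0.20.
- Null SE = √(0.16 × (1/180 + 1/144)) = 0.0447.
- Alternative SE = √(0.2016/180 + 0.09/144) = 0.0418.
- Probability of a significant false benefit = Φ[(0.18 − 1.96 × 0.0447)/0.0418] = Φ(2.21) = 98.6%.

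| Remission of baseline cases | b | i | Probability of a false benefit |
|---|---|---|---|
| None | 20-30% | 5-15% | 95% to >99% |
| 30% | 20-25% | 10-15% | 68-94% |
| 50% | 20-30% | 5-15% | 36-95% |

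The no-remission rows imply control prevalences up to 0.30 + 0.70 × 0.15 = 40.5%, above the protocol's own 20-30%. If prevalence is instead held at 20-30% and the incidence is 10-15%, the probability at 132 per arm is 19-98%.

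**3. Like-for-like power.** Suppose incidence really meant new cases. Let baseline cases persist and the intervention halve new cases (20% to 10%, 25% to 12.5%, or 30% to 15%), with b = 20-30%. The month-36 prevalences then range from 44% vs 32% (b = 20%, 30% to 15%) to 44% vs 37% (b = 30%, 20% to 10%). The formula in step 1 gives 256 to 771 per arm, and power at 200 per arm is about 30-70%.

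**The case against.** A reader might infer that the trial's analysis has a false benefit built in. The documents do not support that. The mixed pair appears only in the sample-size item, and the statistical methods nowhere say that control prevalence will be tested against intervention-arm incidence. The false-benefit probabilities therefore describe an analysis the protocol does not specify.

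Loose wording is also a plausible explanation. The incidence has no time period or at-risk denominator, no rule removes prevalent cases, and 132 is recovered by treating the two rates as like proportions. If incidence meant the proportion expected to have the syndrome at month 36, the arithmetic stands for pairs such as 28% vs 14% and no bias follows.

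Nor does the design rule out a fair comparison: waist circumference, blood pressure, glucose and lipids are all scheduled at month 36 in both arms. The detailed definition of the composite could properly sit in an analysis plan that is not shown.

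All of this stands, and it makes the bias conditional. It does not rescue the sentence. The protocol does not say that incidence means prevalence. An analysis plan could choose a common month-36 measure, but it could not create a control incidence without control baseline data. Even on the charitable reading, 132 fits only part of the stated ranges.

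**Conclusion.** The point holds in a conditional form. The basis for 132 per arm and 80% power is wrong as written, because it pairs a prevalence with an incidence that the control arm cannot supply. An analysis that followed the contrast would have a false-benefit probability far above the nominal level. The figures are 95% to over 99% with no remission and 36-95% with half of baseline cases remitting, given two-sided alpha 0.05, 180 women per arm, baseline prevalence 20-30% and 3-year incidence 5-15%. The size depends strongly on remission, for which the protocol gives no rate.

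The power statement needs repair on either reading. If both figures are month-36 prevalences, 200 per arm gives anything from 26% power (20% vs 15%) to 95% (30% vs 15%), and more for wider gaps within the ranges. If the intervention only halves new cases and baseline cases persist, power at 200 is about 30-70%.

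**What to change.** - Name one compared outcome: prevalence of metabolic syndrome at the month-36 study visit, with the same definition in both arms and all examined women in the denominator.
- Report incidence in the intervention arm descriptively, with no between-arm test.
- Rewrite the sample-size sentence as prevalence versus prevalence, with one stated pair of values, the alpha level and its sidedness.
- Restate the power for the planned 200 per arm and for the number expected after loss. If the intended effect is on new cases only, first convert it to month-36 prevalences, as in step 3 of the working.

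The cost is protocol wording and a recalculation. No added measurements are needed, because every component is already scheduled at month 36 in both arms. The downside is that the stated power may look less favourable once prevalent cases stay in both arms.

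### One power figure (80% at 132 per arm) is stated for two ranges of rates, but it reproduces at 30% v 15%, the upper end of both; at 20% v 10% power is about 62%

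*Protocol*

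**What the plan says.** All of this stands in the protocol under Research design and methods, Overview.

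- **Control rate** (Sampling, size of sample): "With a 20-30% estimated prevalence of metabolic syndrome in people living with HIV", without specific risk-factor intervention.
- **Intervention rate** (same place): "a proposed 10-15% estimated incidence of metabolic syndrome in the intervention arm".
- **Power statement** (same place): "132 participants per arm would allow for 80% power". No pair of rates, significance level, sidedness or test is attached to it.
- **Loss** (same place): "An additional 10% can be added to allow for loss to follow-up".
- **Planned enrolment** (same place): "an intervention arm of 200 women co-enrolled in the PROMOTE study at the Umlazi CRS" and "a control arm of 200 women receiving HIV care at the PHC".
- **Reason for enrolling more than 132**: "The larger proposed sample size will allow for external validity / generalizability". The same sentence appears again under Measures to ensure validity, External.
- **Selection**: by convenience sampling, from a research clinic and a primary health care clinic in Umlazi. The intervention cohort was chosen because the principal investigator works at the research clinic.
- **Test** (Statistical methods): "The categorical variables will be compared using Chi sq or Fisher"'s exact test.

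**The concern.** The number needed for a comparison of two proportions depends strongly on the rates. The two stated ranges allow an absolute difference anywhere from 5 points (20% v 15%) to 20 points (30% v 10%), and no single sample size gives 80% power over that span. Yet the protocol attaches one power to one number without condition.

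This is the protocol's only power statement. A reader who accepts it could treat everything above 132 per arm as surplus and regard heavy loss as harmless. A null result could then be read as evidence against the intervention when, for part of the stated range, the study had limited ability to detect the difference. The stated reason for 200 per arm adds to this, because it presents the extra women as serving generalizability and not power.

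**Working it through.** **Inputs.** The rates (20-30% and 10-15%), 132 per arm, 200 per arm and 10% loss come from the size-of-sample text. Both rates are treated as proportions compared at the end of the study with equal arms. Two-sided 0.05 is an assumption because the protocol states no alpha; one-sided 0.05 is shown as the alternative.

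**Formulas.** With p̄ = (p1 + p2)/2, A = √[2p̄(1 − p̄)], B = √[p1(1 − p1) + p2(1 − p2)] and d = p1 − p2:

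- n per arm = (1.960·A + 0.842·B)² / d²
- continuity-corrected n = (n/4)·[1 + √(1 + 4/(n·d))]²
- power at n per arm = Φ[(d·√n − 1.960·A)/B]

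**Step 1: reproduce 132.** At 30% v 15%, p̄ = 0.225, A = 0.5906, B = 0.5809 and d = 0.15.

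- n = (1.1576 + 0.4889)² / 0.0225 = 120.5, so 121 per arm.
- With continuity correction: (120.5/4)·(1 + √1.2214)² = 133.5, so 134 per arm.
- Exact power of Fisher's test at 132 per arm: 80.5%.

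The stated 132 therefore reproduces at 30% v 15%, within two women of the continuity-corrected figure.

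**Step 2: the lower ends.** At 20% v 10%, A = 0.5050, B = 0.5000 and d = 0.10.

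- Power at 132 = Φ[(0.10 × 11.489 − 1.960 × 0.5050)/0.5000] = Φ(0.318) = 62.5%.
- Other methods at 132: 63.5% by arcsine, 56.9% by Fisher's exact test, 55.7% continuity-corrected.
- One-sided 0.05: 73.8%.
- n needed for 80%: 199 per arm (219 continuity-corrected; 157 one-sided, or 177 one-sided with continuity correction).

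None of these variants gives 132 at 20% v 10%.

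**Step 3: across the ranges.** The n and power columns use the pooled formula. The 180 is 200 × 0.90.

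| Control v intervention | n per arm for 80% | Power at 132 | Power at 132, one-sided | Power at 180 | Power at 200 |
|---|---|---|---|---|---|
| 30% v 10% | 62 | 98.5% | 99.4% | 99.8% | 99.9% |
| 30% v 12.5% | 85 | 94.0% | 97.0% | 98.4% | 99.1% |
| 25% v 10% | 100 | 89.8% | 94.5% | 96.6% | 97.9% |
| 30% v 15% | 121 | 83.5% | 90.2% | 93.0% | 95.2% |
| 25% v 12.5% | 152 | 74.2% | 83.4% | 86.3% | 89.6% |
| 20% v 10% | 199 | 62.5% | 73.8% | 75.9% | 80.2% |
| 25% v 15% | 250 | 52.9% | 65.1% | 66.1% | 70.7% |
| 20% v 15% | 906 | 18.6% | 28.2% | 23.8% | 25.9% |

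On an even grid over the two ranges (two-sided 0.05), about 60% of the pairs fall below 80% power at 132 per arm, about 38% at 180 and about 32% at 200. The grid gives every pair equal weight. It describes the ranges and does not say which pairs are likely.

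**The case against.** The strongest case on the other side has three parts.

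**The number is not miscalculated.** It reproduces at 30% v 15% with a test that the protocol names. The upper end of the control range also has support in the document: the Background and the Literature Review cite a mean prevalence of 30.5% among people living with HIV in Africa. This stands. The defect is a design pair that is not named and a power stated as if it covered both ranges.

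**The study does not stop at 132.** At 200 per arm, the pairs in which the intervention halves the rate all reach 80% (20% v 10% gives 80.2%). After 10% loss, the worst of them falls about four points short. This also stands, and it lowers the severity. It does not repair the text, since the protocol never justifies 200 by power and narrower gaps stay below 80% even with no loss.

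**Alpha and sidedness are not stated**, so 62% is conditional. That is correct. One-sided 0.05 brings 25% v 12.5% above 80% at 132 (83.4%), but 20% v 10% reaches only 73.8%.

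A reader might also infer that 132 per arm is adequate for 30% v 15% and for nothing else. The protocol does not support that. It gives two ranges without pairing their values, and several pairs inside them have a wider gap and exceed 80% at 132: 25% v 10%, 30% v 12.5% and 30% v 10%.

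**Conclusion.** The point holds in a limited form. The protocol claims 80% power at 132 per arm for ranges of 20-30% v 10-15%, but the figure belongs to 30% v 15%. At the lower end of both ranges, power at 132 is about 62% (about 74% if one-sided). Across the ranges it runs from about 19% to 98.5%.

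A reader might go further and conclude that the study as planned is underpowered. The documents do not support that as a general statement. With 200 enrolled and 180 analysed, power is 93% at 30% v 15%, 86% at 25% v 12.5% and 76% at 20% v 10%. Only the narrower gaps are weak: 66% at 25% v 15% and 24% at 20% v 15%.

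The generalizability reason does not hold in either place. More women narrow the uncertainty about the women sampled, but they do not make a convenience sample from two clinics represent a wider population.

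The figures assume two-sided 0.05, equal arms, an unadjusted comparison of proportions and the plan's own 10% loss. Severity is moderate: a figure that readers will rely on needs restating, but no enrolment target, endpoint or analysis changes.

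**What to change.** 1. In the size-of-sample text, name the pair of rates, alpha, sidedness and test behind 132. If the pair was 30% v 15%, say so, without implying that no other pair reaches 80%.
2. Base the power statement on the planned sample. Suggested content, if two-sided 0.05 is confirmed: with 200 women enrolled per arm and 10% lost (180 analysed), power is about 93% for 30% v 15%, 86% for 25% v 12.5%, 76% for 20% v 10% (80% with no loss), 66% for 25% v 15%, 24% for 20% v 15%, and over 99% for 30% v 10%.
3. Remove the sentence that the larger sample gives external validity, both in the size-of-sample text and under Measures to ensure validity, External.

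The cost is one rewritten paragraph and one deleted line. Enrolment stays at 200 per arm. The only downside is a less favourable stated power over part of the range.

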Several studies have shown that majority of the non-nucleoside reverse transcriptase inhibitors (NNRTIs), including current 1^st^ line ART Efavirenz, and NRTIs, currently in use are associated with impaired lipid metabolism whereas the newer ART have not been associated with significant adipocyte dysfunction.

Methods of risk prediction and risk reduction strategies for atherosclerotic CVD in people living with HIV remain a major research gap in developing countries. A recent recommendation by the World Health Organization (WHO) is the provision of a cardiovascular risk assessment in all people living with HIV using standard protocols recommended for the general population. The commonly used cardiovascular risk assessment tools are non-specific to HIV and/or resource-constrained settings. The South African dyslipidaemia guidelines advocate CVD risk assessment at ART initiation by means of the Framingham table which underestimates risk in this population and is non-specific to LMIC. WHO Package of Essential Non-communicable Disease interventions for primary health care in low resource settings (WHO PEN) encompasses the WHO and International Society of Hypertension (WHO/ISH) cardiovascular risk prediction charts which are specific to 14 epidemiological sub-regions, and applying charts for sub-region Afr E would be a more suitable CVD risk assessment tool in our setting. In addition to the risk assessment, the WHO PEN provides concise management guidelines for CVD risk modification.

The association between HIV and CVD risk factors in South Africa has been documented mainly in cross-sectional studies. The WHO PEN is the investigator’s choice of intervention in this proposed prospective study in women who receive HIV care. There are currently no studies assessing the impact of WHO PEN interventions in people living with HIV in resource-constrained settings.

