**Secondary objectives:**

- Compare CVD risk between women receiving Efavirenz versus Lopinavir/r containing ART regimens.

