## CVD risk assessment tools in HIV

A recent recommendation by WHO is the conduct of a cardiovascular risk assessment in PLWH ([40](#_ENREF_40)). The commonly used cardiovascular risk assessment tools do not consider HIV infection, ART type, duration of ART and younger age of PLWH. Cardiovascular risk has therefore been underestimated in PLWH especially younger PLWH ([7](#_ENREF_7)). The most widely used Framingham cardiovascular risk assessment tool has been to some extent, successfully used in PLWH in high income settings, however this tool has does not account for LMIC, and are most often administered in older persons with already well established disease ([41](#_ENREF_41)).

The Data collection on Adverse effects of anti-HIV Drugs (DAD) study includes a coronary heart disease (CHD) equation that calculates the absolute 5-year risk of CHD in PLWH. The DAD equation was developed in high-income countries and utilizes conventional risk factors and ARTs, indinavir, lopinavir/r and abacavir exposure to predict risk of CVD ([42](#_ENREF_42)). In a local study the DAD risk equation demonstrated a 31.1% moderate to high 5 year CVD risk, whereas when applying the Framingham equation only 6.7% moderate to high 10 year CVD risk was seen. Most participants had a low CVD risk by both risk equations in this cross-sectional study in rural SA([30](#_ENREF_30)).

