**Intervention group**: There are 245 HIV infected women between 18 and 49 years of age, who have been on ART for more than 1 year and attending the CAPRISA Research Clinic in Umlazi. These women were enrolled into the PEPFAR PROMise Ongoing Treatment Evaluation (PROMOTE) observational study from May-June 2017. This study has been implemented to provide long-term follow-up data on safety outcomes of widespread use of combination antiretrovirals (cART) among an already well-characterized cohort of HIV infected mothers and their children who previously enrolled in the multi-site PROMISE study. This cohort was selected for the proposed intervention arm because the principal investigator is based at the research clinic. Women will be briefed at their next PROMOTE study visit and the 1^st^ 200 interested candidates meeting all eligibility criteria will be co-enrolled into the Intervention arm of the Sub-study.

**Control group**: The Tier data base will be used to select HIV infected women aged between 18-49 years, receiving ART for more than 1 year at the Umlazi Gateway PHC. Scheduled clinic visits at similar time points to the anticipated clinic visits in the intervention group will be used to establish a list of potentially eligible women. Following a matched pool of data, the first 200 women fulfilling the inclusion criteria, who attend the clinic for their next appointment and who consent to study participation will be enrolled.

1. Data sources

- Intervention group: Each participant in the intervention group will be assigned a new Participant identifier number (PID) in addition to the PROMOTE PID. History taking and physical exam, as well as laboratory results and where applicable ultrasound reports, will be entered directly into a data collection tool on a Microsoft Excel spreadsheet (Appendix I).
- Control group: Participants will be assigned a PID in addition to their clinic chart number. Information from clinic patient medical records will be entered directly into the data collection tool (Appendix II). At the final study visit; history, physical exam, lab report finding and ultrasound findings (where applicable), will be source documented.

1. Measures to ensure validity

- Internal
- The prospective nature of the study, large sample size, careful matching between cohorts by age category and by duration of ART aims to counteract the potential for selection bias.

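### ART regimen is left out of both the matching rule and the confounder list for a non-randomised, two-clinic comparison, although the protocol itself says regimen affects several of the outcomes

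*Protocol*

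**What the plan says.** **Design and matching.** The Protocol's Overview describes a two-arm quasi-experimental study. On sampling it says "Two HIV-infected female cohorts will be matched for receipt of ART duration >1 year and for age will be compared in the study" and "Method of selection will be via convenience sampling". The measures for internal validity repeat the rule: "careful matching between cohorts by age category and by duration of ART aims to counteract the potential for selection bias".

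**Source of the arms.** Intervention women attend a research clinic and come from an "already well-characterized cohort of HIV infected mothers and their children who previously enrolled in the multi-site PROMISE study". Controls come from a public primary care clinic and are treated by its staff under national guidelines.

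**Analysis.** Under Statistical methods, continuous variables are compared by t-test or Wilcoxon test and categorical variables by chi-square or Fisher's exact test. Logistic regression is planned for predictors of cardiovascular disease. The list of possible confounders names the controlled research setting and CD4 count: "These women may have commenced ART with a higher baseline CD4 counts". It then says that multivariable regression will control for confounders, without naming covariates.

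**Regimen elsewhere in the Protocol.**
- Background: most NNRTIs, and NRTIs, "currently in use are associated with impaired lipid metabolism whereas the newer ART have not been associated with significant adipocyte dysfunction".
- HIV and Dyslipidamia: efavirenz raises total cholesterol, LDL and triglycerides; TDF-based treatment had lower lipids than other NRTIs.
- HIV and Hypertension: systolic pressure was lower in people on integrase inhibitors than in those not on them.
- HIV, obesity and insulin resistance: more fat gain with efavirenz than with raltegravir.
- Other risk factors for CVD: a larger hsCRP rise with efavirenz than with other ART.
- CVD risk assessment tools in HIV: the DAD equation "utilizes conventional risk factors and ARTs, indinavir, lopinavir/r and abacavir exposure to predict risk of CVD".
- Secondary objective: "Compare CVD risk between women receiving Efavirenz versus Lopinavir/r containing ART regimens".
- Schedule of evaluations: regimen is recorded in both arms, at the periodic and final time points.
- Table of associations: regimen is crossed with every risk marker.

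**The concern.** A confounder here is a variable that affects the outcome and differs between the arms. The Protocol supplies the first half for regimen, on several outcomes. It does nothing to secure the second half. The arms are one clinic each, chosen by convenience, with different treatment histories, and neither matching variable controls which drugs a woman takes.

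A change-from-baseline analysis would not rescue the comparison for many outcomes. In controls, waist circumference, fasting glucose, hsCRP, urine microalbumin and all three risk scores are scheduled only at the 36-month visit. For these the arm contrast is essentially cross-sectional, so a difference in regimen mix passes straight into it.

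At stake is the first primary objective, the effectiveness of WHO PEN in modifying risk factors. A regimen difference between clinics could appear as a benefit or could hide one.

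**Working it through.** **1. Is regimen controlled anywhere in the arm comparison?**

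| Place in the Protocol | Variables named | Regimen? |
|---|---|---|
| Method of selecting sample | age, ART duration | no |
| Measures to ensure validity, internal | age category, ART duration | no |
| List of possible confounders | research setting, CD4 at ART start | no |
| Multivariable regression | none named | not stated |
| Schedule of evaluations | regimen, both arms | yes, recorded |
| Table of associations | regimen against each marker | yes, as an exposure |

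Regimen is collected and studied, but is not designated as a control variable for the arm contrast.

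**2. The plan's own figure, as a yardstick.** The sample size section gives 132 per arm for 80% power, from 20-30% metabolic syndrome without intervention against 10-15% with it. Two-sided alpha of 0.05 is assumed, because it is not stated. With p1 = 0.30, p2 = 0.15, mean 0.225 and d = 0.15:

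n = [1.960·√(2·0.225·0.775) + 0.842·√(0.30·0.70 + 0.15·0.85)]² / 0.15² = 120.5, or 121.

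With continuity correction: (n/4)·[1 + √(1 + 4/(n·d))]² = 133.5, or 134. This reproduces 132 to within 2%. The planned effect is 10 points (20% v 10%) to 15 points (30% v 15%), taking matching ends of the two ranges.

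**3. Illustration of the bias with no WHO PEN effect.** The documents give neither regimen shares by clinic nor prevalence by regimen, so both are assumed.
- Prevalence is 20% on the less adverse and 30% on the more adverse regimens. This borrows the ends of the plan's overall range, which the plan does not present as regimen-specific.
- The share on the more adverse regimens differs between arms by g, centred on 50%.
- There are 180 completers per arm (200 × 0.90).

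Spurious difference = (0.30 − 0.20) × g. The rejection probability is Φ(δ/SE − 1.96) + Φ(−δ/SE − 1.96), where δ is the spurious difference and SE = √{[pa(1 − pa) + pb(1 − pb)]/180}.

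| g | pa v pb | δ | SE | δ/SE | Chance of p < 0.05 |
|---|---|---|---|---|---|
| 30 points | 23.5% v 26.5% | 3.0 points | 0.0456 | 0.658 | 10.1% |
| 50 points | 22.5% v 27.5% | 5.0 points | 0.0456 | 1.097 | 19.5% |
| 60 points | 22.0% v 28.0% | 6.0 points | 0.0455 | 1.318 | 26.1% |

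The nominal rate is 5%. A difference of 3 to 6 points is between 3/15 = 20% and 6/10 = 60% of the planned effect.

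**4. Wider assumptions.** Take 15-20% prevalence on the lower-risk regimen, a prevalence ratio of 1.5-2.0, and 90% of controls on the higher-risk regimen. With 70%, 50% or 30% of the intervention arm on it, the spurious difference is 1.5-4, 3-8 or 4.5-12 points. The upper ends use 20% with a ratio of 2.0. That puts control prevalence at 0.20 × (1 + 0.9) = 38%, above the plan's 20-30%, so they should be read as extremes. If the intervention arm has more of the higher-risk regimen, the sign reverses.

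**5. DAD.** Because exposure to lopinavir/r, indinavir and abacavir enters the equation, an arm contrast of DAD scores would move with regimen mix even if no conventional risk factor differed.

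**The case against.** The strongest reply is that the Protocol does plan multivariable control, that its list is headed as possible confounders and does not claim to be complete, and that covariates are often named in a statistical analysis plan, which is not at hand. Regimen is also recorded and appears in the association table and the secondary objective. This stands in part: the gap is an unnamed covariate, not an absence of adjustment. It does not remove the point. The Protocol chose to state a matching rule and a list of confounders, and both omit a variable that its own literature review ties to the outcomes.

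Several stronger readings are tempting and are not supported.
- **That a regimen effect could not be separated from WHO PEN.** Regimen is recorded in both arms, so adjustment can separate the two unless regimen nearly coincides with arm.
- **That the clinics differ in regimen.** The documents give no regimen data for either clinic. Different cohort histories make a difference plausible, no more.
- **That the Protocol ties regimen to glucose.** It ties insulin resistance to ART use in general. It also does not say whether efavirenz or lopinavir/r is metabolically worse, and the secondary objective only compares them.
- **That DAD is a between-arm endpoint.** The second primary objective compares risk scores with short-term outcomes in women over 40. The DAD point applies only if scores are compared by arm.
- **That regimen must be matched.** The Protocol does not say that the database used to select controls holds regimen, and matching on a third variable among the first 200 attenders may not be feasible. Adjustment is enough.

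**Conclusion.** The point holds as an omission that is easily repaired. Regimen is neither matched nor listed as a confounder, although the Protocol says it affects lipids, systolic pressure, fat gain and hsCRP and enters DAD. The unadjusted tests, or a model adjusted only for the listed confounders, would attribute part of any clinic difference in regimen mix to WHO PEN.

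Direction and size are unknown. The 3 to 6 points, and the 10% to 26% false-positive risk, show scale under assumed prevalences and shares; they do not estimate the bias in this study. A modest imbalance would matter little, while a large one could imitate a substantial part of the planned effect. Whether that arises depends on an imbalance the documents neither show nor exclude.

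**What to change.** - Add ART regimen class at entry (efavirenz-based, lopinavir/r-based, other) to the list of possible confounders.
- Base the arm comparison of risk factors on a model with arm, entry regimen class and the confounders already planned, with the raw tests as description. Do the same for DAD if it is compared by arm.
- Use regimen at entry. A later regimen may itself follow from risk-factor findings during the study, so adjusting for it could remove part of the intervention's effect. Tabulate switches by arm.
- Tabulate entry regimen by arm, so that readers can see whether there was an imbalance and whether the arms overlap enough for adjustment to work.
- Matching on regimen is optional.

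The cost is a wording change and a few degrees of freedom. No new data are needed, since regimen is already recorded in both arms.
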